#### Covariates

Socio-demographic information about family caregivers and people with dementia will be collected at baseline through a self-designed demographic information sheet which includes the caregiver’s gender, age, employment status, relationship to the care recipient, co-residence with care recipient or not, education background, caring duration and hours spent on care activities. Demographic questions will also ask about the care recipient’s gender, age, duration of dementia, health insurance and living assistance.

#### Economic evaluation

***Quality-adjusted life-years (QALYs):*** The SF-12 will be used to collect data for the QALYs calculation. QALYs will be calculated using the SF-6D preference to estimate the utilities based scoring algorithm developed by Brazier and colleagues [40].
***Health care utilization:*** This proposed study will measure the direct costs related to the family caregiver’s situation and people with dementia. Direct costs will include medications, admissions to hospitals, admission to other institutions, and the number of consultations with health professionals (GP, RN, medical specialist, physiotherapist, etc.). Indirect costs are reduced efficiency at work (presenteeism) and the productivity loss caused by work absenteeism.
***Time spent on caregiving:*** Caregivers will be asked to estimate the total hours spent on providing care for people with dementia in the past week. In addition to this, information of the availability of other informal caregivers will be collected by the research team. The total time the primary family caregiver and other informal caregivers spent on providing care will be recorded and calculated.

### Intervention fidelity

The ITBCS project field officers will receive 12 hours of training to standardize delivery of the ITBCS program prior to participant recruitment. The research team will support and supervise the project field officers while implementing the ITBCS program. To maintain the intervention fidelity, records will be kept by both project field officers and family caregivers of people with dementia including: (1) intervention record-project field officer version; and (2) intervention record-family caregiver version. Compliance with the intervention protocol will be checked by using these two tools. In addition, the study will have a safety officer (SO). The responsibilities of the SO include, but are not limited to, auditing study processes, maintaining data confidentiality and safety, and contingency planning.

### Statistical methods

All data will be double entered into an Excel database on two separate occasions and exported to SPSS software 25.0 for analysis. Internal consistency of the seven instruments will be tested using Cronbach’s alpha coefficient. For the pilot study, paired *t* tests will be conducted to evaluate whether any differences occurred in participants on the seven outcome variables pre- and post-intervention. The research team will perform all analyses of the cluster RCT study based on the intention to treat principle. Baseline data between the experimental and control group will be compared. Missing data will be imputed if deemed necessary. The most appropriate imputation methods will be decided based on the amount and pattern of missing data. A mixed effect model, which takes into account the repeated measurement of outcomes, will be conducted to analyse the primary outcome. The mixed effect model will include treatment, time, and interaction between time and treatment as the fixed effect, baseline measurement of outcome as the covariate, and subject as a random effect. The treatment difference and its 95% confidence interval (CI) will be derived from the mixed effect model. Moreover, adjusted treatment difference will be derived by adding the pre-specified covariates into the mixed effect model. All other outcomes (CES-D, SF-12, SSRS, RSCSE, NPI-Q and DAD) will be analyzed separately using this general framework.

Cost-effectiveness analyses (CEA) and cost-utility analyses (CUA) will be conducted. The difference of total costs among scenarios will first be calculated, which will be further divided by the difference in average effect sizes to estimate the incremental cost-effectiveness ratio. Inflation correction is not necessary as we will evaluate the costs covering 9 months. Multiple imputation methods will be applied to deal with the missing data in the follow-up measurements. A 95% confidence interval of the mean difference in the treatment groups’ total costs will be calculated. Cost-effectiveness acceptability curves will indicate the cost-effectiveness comparison between the ITBCS program and the usual care, with a range of different ceiling ratios presenting decision uncertainties. Furthermore, sensitivity analyses to test the robustness, such as scenarios that vary key variables will be conducted.

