### Sample size

The sample size calculation for the study is based on the primary outcome, “caregiver burden score” measured by the 22-item Zarit Burden Interview (ZBI) scale, and is estimated on the basis of an earlier RCT with a telephone-based multicomponent intervention program for family caregivers of people with dementia [29]. A significant decline of 18.44 in the burden score in the intervention group at post intervention with polled standard deviation of 17.0 were reported. These values will be used to calculate the sample size in the present study. Since randomization will be conducted by community health service centers, the sample size is adjusted by the intra-class correlation coefficient (ICC) to take into account the design effect. The adjustment considered a higher ICC of 0.3 with a design effect of 3.7 for a cluster size of 10 participants in each center. To achieve at least 90% power at a 5% significance level, the required number of centers would be 7, with 70 family caregivers in each group. Assuming an attrition rate of 20%, we will need 84 participants per group or 168 in total.

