### Randomization and allocation concealment

A randomization protocol will be used to select fourteen community health service centers in Hanshou County randomly (http://stattrek.com/statistics/random-number-generator.aspx). There will be seven centers in each group (intervention group and control group). An external biostatistician who will not participate in the study intervention or data analysis will conduct the randomisation. All eligible family caregivers living in the intervention communities will be the intervention participants, while those living in the control communities will be control participants.

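### The primary mixed model has no term for the randomised centre; at the plan's own ICC of 0.3 its nominal 5% test has a type I error of about 31%

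*Protocol article*

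**What the plan says.** The Sample size and Randomization sections make the health service center the unit of randomisation, with seven per group. Sample size pays for this explicitly, using "a higher ICC of 0.3 with a design effect of 3.7 for a cluster size of 10 participants in each center".

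Statistical methods then lists the primary model term by term. The fixed effects are treatment, time and their interaction. The rest of the model is "baseline measurement of outcome as the covariate, and subject as a random effect". Its declared purpose is to handle repeated measurements; clustering is not mentioned. The treatment difference and its 95% confidence interval are taken from this model. The other outcomes (CES-D, SF-12, SSRS, RSCSE, NPI-Q and DAD) "will be analyzed separately using this general framework".

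The article mentions no random centre effect, GEE by centre, cluster-robust variance or centre-level analysis. The Covariates section does not list centre either, so the covariate-adjusted version of the model has the same gap.

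**The concern.** A random subject intercept describes how one caregiver's scores at 3, 9 and 15 months hang together. It says nothing about two caregivers from the same centre, whom the model takes as independent. The sample-size section assumes the opposite. Shared local conditions make within-centre correlation plausible, and in the intervention arm so do shared field officers (four per centre, each with three caregivers).

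Treatment varies only between centres, so its precision is governed by how much centres differ and by how many there are. If that variation is left out, the standard error is too small, the 95% interval covers too seldom, and chance differences between seven centres and seven others can pass for a treatment effect. This affects the primary hypothesis and every secondary outcome. The design also becomes inconsistent with itself: the trial is enlarged 3.7-fold for clustering and then analysed as if there were none.

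**Working it through.** **Inputs, all from Sample size unless noted.** Difference 18.44 ZBI points ("A significant decline of 18.44 in the burden score in the intervention group at post intervention"); SD 17.0; ICC ρ = 0.3; m = 10 per centre; 7 centres per arm; 5% significance, taken as two-sided because the article does not say; at least 90% power. The primary time point, 15 months adjusted for baseline, comes from Primary outcomes.

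**1. The plan's own figure.** Under independence, n per arm = 2 × (1.960 + 1.282)² × 17.0² / 18.44² = 17.86, so 18. The design effect is DE = 1 + (m − 1)ρ = 1 + 9 × 0.3 = 3.7, and 18 × 3.7 = 66.6, which rounds up to 7 centres of 10 = 70 per arm. The stated figure reproduces, with normal-approximation power of 91.6%.

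**2. Standard error of the 15-month difference, without baseline adjustment.**
- Caregivers taken as independent: 17.0 × √(2/70) = 2.87 points.
- Clustering included: 2.87 × √3.7 = 5.53 points.
- Ratio: √3.7 = 1.92.

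**3. Type I error of a nominal two-sided 5% test that ignores centre:** 2 × [1 − Φ(1.96/√DE)]. At DE = 3.7 this is 2 × [1 − Φ(1.02)] = 30.8%, so a nominal 95% interval covers about 69% of the time. After the planned 20% attrition, 84 per group becomes 67.2, or 9.6 per centre; DE is then 1 + 8.6 × 0.3 = 3.58 and the error 30.0%.

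**4. Simulation of the stated model under the null.** Each setting used 2,000 trials, 14 centres of 10, three follow-ups, a baseline covariate and a random subject intercept, with treatment tested at the third follow-up. The article gives no baseline-to-follow-up correlations, so these were varied: 0.3 to 0.7 for individuals and 0 to 0.95 for centres.

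| ICC | DE (m = 10) | SE ratio | Type I error, formula | Type I error, simulated |
|---|---|---|---|---|
| 0.01 | 1.09 | 1.04 | 6.0% | 4–8% |
| 0.02 | 1.18 | 1.09 | 7.1% | not run |
| 0.05 | 1.45 | 1.20 | 10.4% | 6–20% |
| 0.10 | 1.90 | 1.38 | 15.5% | 8–29% |
| 0.20 | 2.80 | 1.67 | 24.1% | not run |
| 0.30 | 3.70 | 1.92 | 30.8% | 16–41% |

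The low end of each simulated range arises where centre differences persist strongly from baseline, so that the covariate absorbs much of them. The high end arises where they do not persist: the covariate then removes individual variation and leaves centre variation in place. With ICC 0 the simulated error is 4–6%, as it should be.

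**5. An analysis that respects centre.** A t-test at centre level on 14 − 2 = 12 degrees of freedom gave 4.8% to 6.4% in the same ICC 0.3 simulations.

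**6. Price in power.** With 70 per arm, DE 3.7 and t on 12 df, power for 18.44 points is about 86%, against 91.6% by the normal approximation.

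**The case against.** The best defence is that an article condenses. The sentence says what the model will include without claiming to be exhaustive, the sample-size section shows that the team knows about clustering, and a full analysis plan could add centre without contradicting the text. This carries little weight. The article does not leave the random part open: it names subject as the random effect and repeated measurement as the reason for the model. Someone who programs it as written will omit centre.

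The second objection is about size, and it partly stands. The protocol itself calls 0.3 a higher value, which suggests a cautious planning figure. The documents do not establish the true ICC; at 0.01 or 0.02 the inflation is slight. The simulated ranges also rest on correlations that the protocol does not supply. The 31% should therefore always be quoted with its condition, ICC 0.3.

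Third, the article states no degrees-of-freedom method and no method for the interval of the cost difference. Both are details that an analysis plan may settle. They belong in the remedy and are not errors in the text.

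**Conclusion.** The concern holds. The stated primary model omits the unit of randomisation and contradicts the basis on which the trial was sized. At the plan's ICC of 0.3 and 10 caregivers per centre, the standard error is 1.92 times too small and the type I error is about 31%, roughly six times nominal. Baseline adjustment changes this to between 16% and 41%, depending on assumed correlations, and so cannot be relied on to remove the problem. At an ICC of 0.05 the error is still about double the nominal level; only near 0.01 does the omission become minor. The closed-form figures assume equal centre sizes and a two-sided test. All six secondary outcomes inherit the fault. It must be corrected before the analysis.

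**What to change.** In Statistical methods, replace the random part with: community health service center as a random effect, and subject nested within center as a random effect. State that the 15-month treatment contrast will be tested with a small-sample correction (Satterthwaite or Kenward-Roger, about 12 df). Pre-specify a t-test of the 14 baseline-adjusted centre means as a check, or use it as the main analysis. Apply the same structure to the covariate-adjusted model and to all six secondary outcomes, and let the interval for the cost difference allow for centre too.

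Entering centre as a fixed covariate is not an alternative, because each centre lies wholly in one arm and centre would be confounded with treatment. If centre differences may change over time, a centre-by-time random term is also needed; the centre-mean check at 15 months guards against leaving it out. The error rate in step 5 of the working was obtained for the centre-level t-test. The mixed model with a random centre effect was not simulated and should be checked before it is adopted.

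The edit is one sentence and one extra random term in the program. Intervals become wider, and power on the plan's assumptions is about 86%, below the 90% stated. The investigators should know this early; the article expected recruitment to start by the end of December 2021, after its publication.

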### Variables and measurements

Outcomes will be measured in both groups at baseline (T-0), immediately after main ITBCS (T-1), 9 months post-intervention (T-2), and 15 months post-intervention (T-3). Research assistants blinded to the group assignments will be responsible for collecting all the measures employed in the proposed study.

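### The only estimator stated for the cost-utility analysis reads as a difference of arm averages with no baseline-utility adjustment, although baseline SF-12 is collected and the clinical outcomes are baseline-adjusted

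*Protocol article*

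**What the plan says.** The Statistical methods section of the protocol article describes two separate estimators.

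- **Clinical outcomes.** A mixed model for repeated measurements has treatment, time and their interaction as fixed effects, with "baseline measurement of outcome as the covariate, and subject as a random effect". The treatment difference and its confidence interval come from that model. The section then adds: "All other outcomes (CES-D, SF-12, SSRS, RSCSE, NPI-Q and DAD) will be analyzed separately using this general framework".
- **Economic outcomes.** The next paragraph states: "The difference of total costs among scenarios will first be calculated, which will be further divided by the difference in average effect sizes", which gives the incremental cost-effectiveness ratio. It adds multiple imputation, a confidence interval for the mean difference in total costs, acceptability curves and sensitivity analyses. It mentions no model and no covariate.

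Under Economic evaluation, "The SF-12 will be used to collect data for the QALYs calculation", with utilities scored by the SF-6D. Under Variables and measurements, "Outcomes will be measured in both groups at baseline (T-0), immediately after main ITBCS (T-1" and at two later visits. A baseline utility will therefore exist for each caregiver with a scorable SF-12.

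On the design, "There will be seven centers in each group (intervention group and control group"; the sample size section assumes "a higher ICC of 0.3 with a design effect of 3.7 for a cluster size of 10 participants in each center".

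**The concern.** A QALY total accumulated from baseline contains the baseline utility itself, and later utilities tend to track it. If one arm happens to start with higher caregiver utility, a plain difference in mean QALYs counts part of that head start as programme effect. The difference is the denominator of the cost-utility ratio, where small shifts matter, and it also drives the acceptability curve.

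The article guards against this for the clinical scales. It lists the SF-12 among them, but not QALYs or SF-6D utility. The listing does not settle the matter: the clinical framework is a repeated-measures model with time and time-by-treatment terms, and it cannot be carried over unchanged to one cumulative value per person.

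Cost-effectiveness is a stated aim in the Abstract and Discussion, and only 14 centres are randomised, so chance imbalance is a practical possibility.

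**Working it through.** **1. The plan's own figure.** The article gives no figure for utility or QALYs. The nearest is the sample size, which supplies the design. Its inputs are in the Sample size section: "A significant decline of 18.44 in the burden score in the intervention group at post intervention with polled standard deviation of 17.0 were reported", 90% power, 5% significance (taken as two-sided), ICC 0.3 and 10 caregivers per centre.

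- Individually randomised n per arm = 2 × [17.0 × (1.960 + 1.282) / 18.44]² = 17.9, rounded up to 18.
- Design effect = 1 + (10 − 1) × 0.3 = 3.7.
- 18 × 3.7 = 66.6, i.e. 6.66 centres, rounded up to 7 centres and 70 caregivers per arm. This matches the article; the normal-approximation power at 70 per arm is 91.6%.

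**2. Size of a chance baseline gap.** In SD units of baseline utility, the SE of the arm difference is √(2 × design effect / 70). The ICC of 0.3 was set for the burden score, so a lower value is shown as well.

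| ICC for utility (assumed) | Design effect | SE of gap (SD) | P(gap > 0.25 SD, either direction) |
|---|---|---|---|
| 0.3 | 3.7 | √(7.4/70) = 0.325 | 44% |
| 0.05 | 1.45 | √(2.9/70) = 0.204 | 22% |

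**3. Share of a gap that reaches the QALY difference.** The documents give no between-visit correlation and no rule for turning utilities into QALYs. Assumptions: trapezoidal QALYs; visits at 0, 3, 9 and 15 months after baseline, as in the Abstract and Intervention sections (Variables and measurements words the last two as post-intervention); unit SD at each visit; and one correlation ρ between all visits, equal at person and centre level.

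- Weights over 15 months: 0.125, 0.375, 0.50, 0.25 years (sum 1.25).
- Weights over 9 months, the only economic horizon stated (for costs): 0.125, 0.375, 0.25 years (sum 0.75).
- Pass-through per unit gap = 0.125 + ρ(T − 0.125) years, where T is the horizon in years. Dividing by T gives the share.

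**4. Variance removed by adjustment.** R² = (pass-through)² / Var(QALY), where Var(QALY) = Σw² + ρ(T² − Σw²). Here Σw² is 0.21875 for 9 months and 0.46875 for 15 months.

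| Horizon | ρ | Pass-through (years) | Share of gap | Var(QALY) | R² |
|---|---|---|---|---|---|
| 9 months | 0.3 | 0.3125 | 42% | 0.322 | 30% |
| 9 months | 0.5 | 0.4375 | 58% | 0.391 | 49% |
| 9 months | 0.7 | 0.5625 | 75% | 0.459 | 69% |
| 15 months | 0.3 | 0.4625 | 37% | 0.797 | 27% |
| 15 months | 0.5 | 0.6875 | 55% | 1.016 | 47% |
| 15 months | 0.7 | 0.9125 | 73% | 1.234 | 67% |

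**5. Does the gain survive with 14 centres?** R² ignores the cost of estimating the slope. In a simulation of 20,000 trials (7 v 7 centre means, 10 per centre, ICC 0.3, ρ = 0.5, 15 months), the empirical SE was 0.33 unadjusted and 0.25 adjusted, about 24% smaller. The large-sample formula gives 1 − √(1 − 0.465) = 27%. Most of the gain remains.

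**The case against.** The strongest reply is that the article never calls the QALY difference raw or unadjusted. A ratio of a cost difference to an effect difference is the generic definition of an ICER, and it could be filled with a model-based effect. The SF-12 is baseline-adjusted by name in the preceding paragraph, and a list of scales would not be expected to name a derived quantity. A condensed article may also leave the QALY regression to a fuller plan.

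Much of this stands. Had the article merely been silent, there would be no point to raise. But it does fix a formula, in terms of averages and mean differences, and the formula does not refer back to the clinical model. An analyst following it as written would compare arm means.

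Three stronger readings are tempting, and the documents do not support them:

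- *The plan has decided on a raw difference.* That is the natural reading, not a stated choice.
- *A baseline gap passes straight through.* Under the assumed correlations about 37% to 75% does; all of it would pass only at ρ = 1.
- *The QALY estimate is biased.* Under randomisation the unadjusted difference is unbiased over repeated trials. What it lacks is precision and protection in the one trial that is run.

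It is also true that the 44% figure depends on carrying a deliberately high ICC from the burden score to utility. At an ICC of 0.05 it halves.

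**Conclusion.** The point holds in a limited form. The one estimator stated for cost-utility carries no baseline adjustment on its natural reading, while the adjacent clinical estimator does, and the covariate needed is already being collected. Adjustment is the better method at almost no cost, so the text should be changed.

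The size is moderate and rests on assumptions. The range of ICC for utility (0.05 to 0.3), the correlations (0.3 to 0.7) and the trapezoidal QALYs are not in the documents. Within that range the conclusion is the same for the 9-month and the 15-month horizon. No corrected ICER can be computed, because the article gives no utility SD, correlation or costs. It states no power for QALYs either, so no power gain is claimed.

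**What to change.** In the cost-effectiveness paragraph of Statistical methods, add:

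> The incremental QALY will be estimated by regression of QALYs on treatment arm and baseline SF-6D utility, allowing for clustering by centre (random centre effect or centre-level analysis), and this adjusted estimate will be used in the ICER and the cost-effectiveness acceptability curves.

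The centre term is needed: a regression on arm and baseline utility alone would ignore the clustering that makes a sizeable gap plausible. For the cost-effectiveness (non-QALY) ratio, state that the effect difference comes from the baseline-adjusted clinical model. If a fuller plan already specifies this, align the published formula with it.

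The cost is one sentence, one covariate and, in a centre-level analysis, one degree of freedom (11 instead of 12). No new data are needed, and recruitment had not begun when the article was published. A matching adjustment of costs for baseline resource use is not proposed, because the documents do not show that it is recorded.

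### The incremental cost is described only as a difference in total costs; with 7 v 7 centres it should be adjusted for baseline care hours (and baseline service-use cost, if collected), with centre accounted for

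*Protocol article*

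**What the plan says.** The economic paragraph of Statistical methods builds the ratio in two steps. For the numerator, "The difference of total costs among scenarios will first be calculated". That figure is the one "which will be further divided by the difference in average effect sizes to estimate the incremental cost-effectiveness ratio". Uncertainty in the numerator is given by "A 95% confidence interval of the mean difference in the treatment groups", in terms of total costs. Multiple imputation and acceptability curves are also planned. On robustness, the text says that "sensitivity analyses to test the robustness, such as scenarios that vary key variables will be conducted". No baseline term, covariate or regression is named for costs.

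The preceding paragraph of the same section handles the clinical outcomes differently. The mixed model has "baseline measurement of outcome as the covariate, and subject as a random effect", and a further analysis adds pre-specified covariates. The model is stated for the primary outcome (the Zarit burden score) and is extended to CES-D, SF-12, SSRS, RSCSE, NPI-Q and DAD. Costs are not on that list.

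On baseline data, the Covariates section lists what the baseline sheet collects about the caregiver, including "education background, caring duration and hours spent on care activities". The Economic evaluation section lists medications, admissions and consultations, but gives no time point for them. It treats caregiving time under its own heading: "The total time the primary family caregiver and other informal caregivers spent on providing care will be recorded and calculated". It does not say that these hours are given a money value.

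**The concern.** Families who use much care and many services at entry tend to remain heavy users. If one arm happens to draw heavier-use centres, part of that difference reappears in follow-up cost. An unadjusted difference in totals includes it. The plan deals with this for every clinical scale by conditioning on the baseline value, but states nothing equivalent for cost.

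The incremental cost enters the cost interval, the cost-effectiveness and cost-utility ratios, and the acceptability curves. Adjusting QALYs for baseline utility would not help here, because that changes only the denominator of the cost-utility ratio. Cost-effectiveness is one of the trial's declared aims, and the Randomization section describes 14 randomised centres without stratification or matching.

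**Working it through.** **The plan's own figure.** The protocol gives no figure for costs. Its sample size for the burden score does reproduce: 2 × [17.0 × (1.960 + 1.282) / 18.44]² = 17.86 per arm; design effect 1 + 9 × 0.3 = 3.7; 17.86 × 3.7 = 66.1, or 6.6 centres of 10, rounded up to 7 centres and 70 caregivers. The design is therefore 7 v 7 centres. With 84 enrolled per arm, each centre has 84 / 7 = 12.

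**Inputs for the chance gap.** From the protocol: 7 centres per arm and 12 caregivers per centre. Assumed: an ICC for the baseline cost driver of 0.05 to 0.3. The upper value is the protocol's own, but it was set for the burden score and is described there as high.

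**Formula.** In patient-level SD units, SD of gap = √{2 × [ICC + (1 − ICC)/12] / 7}. For ICC 0.05: √{2 × (0.05 + 0.0792) / 7} = √0.0369 = 0.19. The chance of a gap beyond 0.25 SD in either direction uses a normal approximation.

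| Assumed ICC | SD of gap | P(gap beyond 0.25 SD) |
|---|---|---|
| 0.05 | 0.19 | 0.19 |
| 0.10 | 0.22 | 0.26 |
| 0.30 | 0.32 | 0.43 |

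With 10 per centre, the SDs are 0.20, 0.23 and 0.33, so cluster size hardly matters.

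**Carry-over into cost.** If the baseline driver correlates r with follow-up cost, a gap of g SD shifts the cost difference by about r × g. A gap of 0.25 SD shifts it by 0.4 × 0.25 = 0.10 SD at r = 0.4, and by 0.7 × 0.25 = 0.175 SD at r = 0.7.

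**Gain from adjustment.** The standard error is multiplied by about √(1 − r²), taking r to be the same within and between centres.

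| Assumed r | Fall in standard error, 1 − √(1 − r²) |
|---|---|
| 0.3 | 5% |
| 0.4 | 8% |
| 0.5 | 13% |
| 0.7 | 29% |

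Correlations of 0.4 to 0.7 are plausible assumptions for baseline cost against follow-up cost. Nothing in the protocol supports them for care hours against total cost.

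**Why centre must be in the model.** A patient-level regression that ignores centre understates the standard error by a factor √(1 + 11 × ICC): √1.55 = 1.24 at ICC 0.05 and √4.3 = 2.07 at ICC 0.3. That error is larger than the gain from adjustment over most of these ranges.

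**The case against.** The strongest objection is that this is a condensed article. A difference in total costs defines the numerator of the ratio without saying how it is estimated, and an economic analysis plan could specify a regression. A reader might infer that the trial has committed itself to a raw comparison. The text does not support that: neither the word nor an exclusion of adjustment appears. What stands against the objection is that the section does state an estimator and an interval for costs, directly after limiting its baseline-adjusted model to named clinical scales. The point is thus a better method for a stated analysis, not a complaint about missing detail.

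Secondly, a reader might infer that a chance gap would bias the result or be reported as an effect of the programme. That goes too far. Over random allocations the unadjusted difference is unbiased, provided recruitment within centres does not depend on arm. Chance imbalance is part of what a correct confidence interval expresses, and the plan has an interval, acceptability curves and a comparison of baseline data. What remains is lost precision, and an estimate that is left shifted when an imbalance is actually seen.

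Thirdly, a reader might infer that service use is already collected at baseline. Only care hours are documented at baseline. The Variables and measurements section places outcomes at T-0, but the outcomes then listed are clinical scales. This part of the objection stands, and it limits both the remedy and the gain that can be claimed.

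**Conclusion.** The point holds as a recommendation on method. The cost comparison is described without the baseline adjustment that the same section gives the clinical outcomes, although at least one plausible cost predictor is collected at entry. With 7 v 7 centres, a chance baseline gap beyond a quarter of an SD would occur in roughly 19% to 43% of allocations for an assumed ICC of 0.05 to 0.3. The 8% to 29% fall in standard error applies only if baseline cost is available and correlates 0.4 to 0.7 with follow-up cost. With care hours alone the gain is probably smaller, and the documents do not allow it to be sized. No cost SD, cost ICC or correlation is given, so these figures show a range and do not predict the trial's result.

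**What to change.** In the economic paragraph of Statistical methods, state that the incremental cost will be estimated from a regression of total cost on arm, with baseline care hours as a covariate and baseline service-use cost added if it is collected at T-0. State that centre is accounted for, by a random effect or by a cluster-robust method with a small-sample correction suited to 14 centres. Use the adjusted difference for the cost interval, the ratios and the acceptability curves, and report the unadjusted difference descriptively. The Economic evaluation section should also say whether service use is recorded at T-0.

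Adjusting for care hours costs a sentence or two and needs no new data. If service use is not at present recorded at T-0, adding it would mean further items at an existing assessment, but no extra visits or participants. According to the Trial status section, recruitment had yet to start when the article was written, so the article itself showed no obstacle to fixing this before data collection.
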